### Randomisation and blinding

The present study is a protocol for a single-blind randomised controlled trial in which each group of participants is exposed to only one of the study interventions. Patients will be randomly allocated to robotic-assisted TKA or to conventional freehand TKA. All patients in whom a TKA is indicated will be sequentially allocated in a 1:1 ratio to surgeons who perform robotic-assisted TKA or to those who perform conventional freehand TKA at the time of their outpatient appointment. All patients, irrespective of their allocation, will follow the same clinical, imaging, and anaesthesiologic pre- and post-surgical pathways. Patients will be blinded to the allocation until the first postoperative days. Surgeons and personnel involved in the clinical management of the patients will be unblinded to the allocation. Data curacy and collection will be conducted by two assessors blinded to group allocation and not involved in the clinical management of the patients. Assessors will retrieve patient data at the following follow-up times: admission, perioperatively (from access to discharge), at 6 weeks, 12 months, and every 24 months postoperatively. Data from patients will be collected once the learning curve has been reached.

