### Sample size evaluation

Assuming a true difference in means between the test and the reference group of 5 units, and a pooled standard deviation of 20 units, the study would require a sample size of 198 patients for each group (i.e. a total sample size of 396, assuming equal group sizes), to achieve a power of 80% and a level of significance of 5%, for declaring that the robotic TKA is superior to traditional TKA at 10 units margin of superiority, assuming a minimum clinically important difference for the WOMAC total subscale after TKA of 10 points [22].

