### Statistical analysis

All statistical analyses will be conducted by the main author (FM). For descriptive statistics, arithmetic mean and standard deviation shall be used. The unpaired t-test will be performed to assess baseline comparability, with values of *P* > 0.05 considered satisfactory. Data items will be collected by the assessors prospectively and entered into Microsoft Excel Spreadsheet Software version 2020 (Microsoft Corporation, Redmond, US). To compare robotic TKA versus freehand TKA, the IBM SPSS version 25 will be used. For continuous and binary data, the mean difference (MD) and odds ratio (OR) effect measures will be used. Standard error and 95% of confidence interval will be also evaluated. The null hypothesis will be that no difference between the two techniques exists. Both *χ*^2^ and unpaired *t*-test will be performed to evaluate whether the null hypothesis can be refused. Values of *P* < 0.05 were considered statistically significant. To evaluate the accuracy of implant positioning of robotic versus conventional TKA with regards to the pre-operative planning the standard deviation from the optimal implant alignment according to the patient anatomy will be evaluated using the IBM SPSS version 25.

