Approximately 2000 TKAs are performed each year at our institution, which has been accredited by “Endocert” since 2016. The EndoCert initiative represents the first worldwide certification system of medical centres for total joint replacement and was established in Germany in 2012. The EndoCert aims to maintain quality standards in primary and revision arthroplasty. The associated centres also develop and define standards as well as treatment processes, and they are subject to continuous re-certification [29, 30]. All surgeries shall be conducted by six surgeons in a highly standardized fashion. All surgeons have obtained the certificate of the senior operator of EndoCert, and are well beyond their learning curve, having each performed more than 250 knee arthroplasties.

Some limitations of the present protocol must be acknowledged. The use of the CORI system during TKA requires special instrumentation, training and organisation. Surgery with CORI might initially require a longer time, and the surgical slots will be reserved for a longer time. Therefore, the healthcare staff involved in the clinical management of the patients will not be blinded, increasing the risk of performance bias. Patients will be informed in regard to the nature of the surgery (freehand or robotic) during their postoperative inpatient stay. According to current German legislation, all patients will receive a discharge letter with a description of the surgical intervention. In this instance, patients will have to be aware of their allocation, impacting on detection bias. The Likert-like questionnaire used in the present study is routinely administered at our institution to patients who undergo TKA to rate the function of the knee. Investigations are ongoing to validate this questionnaire in the clinical setting.

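### As written, surgeon appears nested in technique, so the comparison mixes the two, and the planned t-test and chi-square are too optimistic if outcomes vary between surgeons

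*Protocol article*

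**What the plan says.** Three parts of the protocol article bear on this.

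- **Randomisation and blinding.** Patients are "sequentially allocated in a 1:1 ratio to surgeons who perform robotic-assisted TKA or to those who perform conventional freehand TKA". What is assigned is a type of surgeon, and the technique follows from that.
- **Discussion.** "All surgeries shall be conducted by six surgeons in a highly standardized fashion". They hold a senior-operator certificate and are described as "having each performed more than 250 knee arthroplasties". The split of the six between the techniques is not given, nor is it said whether any surgeon does both.
- **Statistical analysis.** The null hypothesis is that the two techniques do not differ. Chi-square and unpaired t-tests "will be performed to evaluate whether the null hypothesis can be refused", with P "< 0.05 were considered statistically significant". Of the mean difference and odds ratio it adds: "Standard error and 95% of confidence interval will be also evaluated".

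Sample size evaluation plans "a total sample size of 396, assuming equal group sizes", with no allowance for surgeon. The article mentions no surgeon term, stratification by surgeon, clustering or ICC.

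**The concern.** There are two linked problems, and they arise in different places.

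1. **Confounding, from the allocation.** If one set of surgeons does robotic TKA and another does freehand TKA, the arms differ by surgeon as well as by technique. Randomising patients balances patients, not surgeons. Recruiting more patients under the same surgeons does not remove the difference.
2. **Standard error, from the analysis.** Patients of one surgeon share whatever that surgeon contributes to outcome. The t-test and chi-square treat all 396 patients as independent, so their standard errors are too small whenever surgeons differ.

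At stake is whether a significant result can be read as an effect of the robot. The issue touches every between-arm comparison in the plan.

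**Working it through.** **Inputs from the article (Sample size evaluation; Discussion):** 198 per group, SD 20, assumed difference 5, margin 10, power 80%, significance level 5% (sidedness not stated), six surgeons.

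**Inputs assumed:** 3 surgeons per arm with 198/3 = 66 patients each, and a range of ICCs, since the documents give neither.

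**Step 1. Reproduce the plan's figure.** Take the distance |5 − 10| = 5 and a one-sided 5% level:

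n = 2 × (1.645 + 0.842)² × 20² / 5² = 197.8, so 198 per group.

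This matches "a sample size of 198 patients for each group". It holds only for independent patients. (That the assumed difference lies below the margin is a separate matter.)

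**Step 2. Standard error used by the t-test.** 20 × √(2/198) = 2.01. The 95% half-width is 1.96 × 2.01, about 3.9 points.

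**Step 3. Standard error with surgeon nested in arm.** Design effect DE = 1 + (66 − 1) × ICC. True SE = 2.01 × √DE. True two-sided type I error of the ordinary test = 2 × [1 − Φ(1.96/√DE)]. Half-width with surgeon as the unit = t(0.975, 4 df) × true SE = 2.776 × true SE, where 4 df = 6 surgeons − 2 arms.

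| ICC | DE | True SE | Type I error | Half-width on 4 df |
|---|---|---|---|---|
| 0 | 1.00 | 2.01 | 5% | 5.6 |
| 0.005 | 1.33 | 2.31 | 9% | 6.4 |
| 0.01 | 1.65 | 2.58 | 13% | 7.2 |
| 0.02 | 2.30 | 3.05 | 20% | 8.5 |
| 0.05 | 4.25 | 4.14 | 34% | 11.5 |

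Simulating the planned t-test (40,000 trials per setting) gave 5.0%, 12.7%, 20.0% and 34.5% at ICC 0, 0.01, 0.02 and 0.05. A separate simulation gave 9.0% at 0.005.

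**Step 4. Other splits.** At ICC 0.05 the type I error is about 36% for 2 against 4 surgeons and 46% for 1 against 5.

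**Step 5. Power for the 5-unit distance, one-sided 5%, 3 against 3.** The normal approximation gives 80% at ICC 0, 61% at 0.01, 50% at 0.02 and 33% at 0.05. On 4 df (non-central t with non-centrality 5 / true SE) it is 66%, 48%, 39% and 26%. Part of the loss therefore comes from having only six surgeons, even at ICC 0.

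**Step 6. Would more patients help?** With k = 3 surgeons per arm, the number needed per arm is 198 × 3 × (1 − ICC) / (3 − 198 × ICC). At ICC 0.01 this is 588.06 / 1.02 = 576.5, so 577 (normal approximation). At ICC 0.02 the denominator is 3 − 3.96, which is negative, so 80% power cannot be reached with any number of patients.

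**The case against.** The strongest reply has three parts.

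- **Nesting is inferred.** A reader might conclude that no surgeon does both techniques. The article does not say so. The allocation sentence describes two groups of surgeons, which favours nesting, but does not expressly exclude overlap. If some surgeons do both, the figures above do not apply as they stand. This limits the claim, and the ambiguity itself needs resolving.
- **Surgeons may differ little.** All are certified and experienced, and approach, implant, cement and rehabilitation are common to both arms. Data are collected only after the learning curve. A reader might infer that the 5% error rate certainly fails. It does not fail at ICC 0, and these features may push the ICC towards the low end of the range. They do not show that it is zero, and they do not separate surgeon from technique. The learning-curve plateau is defined by operating time, not by patient outcome.
- **The target may be these six surgeons.** For a comparison of care as given by these two groups of surgeons, patient-level tests can be valid. But the stated null hypothesis is about the two techniques, so this narrows the conclusion and does not rescue it.

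A reader might also infer that surgeons chose the robot themselves and that a positive result would reflect that choice. The article does not say how surgeons came to a technique, so this is unsupported.

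Nor can the point be left to a fuller analysis plan: the article itself fixes both the allocation and the tests.

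**Conclusion.** The point holds in conditional form. As written, surgeon appears nested in technique, and the analysis ignores it. The direction is firm: for any ICC above 0, P values and 95% intervals about the techniques are too optimistic. The size is not firm. It rests on an assumed 3/3 split with 66 patients per surgeon and an assumed ICC. Over ICC 0.005 to 0.05, the true type I error runs from about 9% to 34%. The reported half-width of about 3.9 points compares with 6.4 to 11.5 on 4 df, against the 10-point minimum clinically important difference that the article cites.

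The source is the allocation rule. The choice of tests carries it into the results. A reader might infer that a mixed model would cure the problem. It would give honest intervals, but under nesting no model can separate surgeon from technique.

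**What to change.** 1. In Randomisation and blinding, state whether each surgeon does one technique or both, and how the six are divided.
2. **Preferred, where surgeons are trained in both techniques:** randomise patients within surgeon, stratify by surgeon, and include surgeon as a fixed effect in the Statistical analysis section (linear model for continuous outcomes, logistic for binary).
3. **If surgeons stay nested:** replace the t-test and chi-square by models with a surgeon random effect and small-sample degrees of freedom (about 4). Describe the contrast as surgeon plus technique, and restate the power. A fixed surgeon effect is not an option here, because it cannot be separated from technique.

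**Cost.** Crossing surgeons changes scheduling and may need further robotic training. Patient volume is unlikely to be the obstacle, at about 2000 TKAs a year against 396 needed. Keeping surgeons nested needs only a change of model and wording, but the price is information: intervals widen, and power at the plan's own 5-unit distance (one-sided 5%) falls from the stated 80% to about 48% at ICC 0.01 and 26% at ICC 0.05 on 4 df.

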### Data to be collected

On admission, the demographic information (age at surgery, BMI, sex), stage of OA according to the Kellgren-Lawrence classification [16], PROMs, and blood values of each patient will be collected on admission. Concerning the blood values, the haematocrit, haemoglobin, and C-reactive protein (CRP) will be collected preoperatively, on the first and fifth postoperative days. The blood tests will be conducted on admission, postoperative day (POD) 1 and 5 by dedicated healthcare personnel. To assess ROM, the neutral-zero method shall be used [17], using a standard baseline plastic 360-degree plastic pocket goniometer with flexion-hyper extension gauge (ProHealthcareProducts.com, Park City, US). ROM surgery will be assessed by moving the foot from a neutral starting position (neutral position in extension) in flexion and extension. ROM data will be collected on admission, on POD 1, 2, 3, 4, 5, and at each follow-up appointment by medical personnel who has not performed the index surgery. The German version of the Western Ontario and McMaster Universities Osteoarthritis Index (WOMAC) [18] and the visual analogue rating scale of health-related quality of life [19] will be used to rate the clinical outcomes. The patients will complete the questionnaires at admission and at each post-operative follow-up appointment. To evaluate the activity level of the patients included in the trial, the German version of the Tegner score will be administered [20]. In addition, a further seven questions Likert-like questionnaire shall be administered to all patients. This questionnaire is routinely used at our institution to rate the function of the knee in patients who undergo TKA. The questionnaire enquires about the activities related to the knee, post-operative overall patient satisfaction, patient satisfaction with the function of the knee, and information concerning walking distance. The Likert-like questionnaire is reported in Fig. 3, and the German version is available in Additional file 1.

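### The only test named for the repeated patient-reported scores is an unpaired t-test, which ignores admission and earlier values: it is less efficient, and on observed data alone it is open to bias if loss depends on outcome and differs by arm

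*Protocol article*

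**What the plan says.** **Data.** Under Data to be collected, "The patients will complete the questionnaires at admission and at each post-operative follow-up appointment". The schedule under Randomisation and blinding is "admission, perioperatively (from access to discharge), at 6 weeks, 12 months, and every 24 months postoperatively". Each patient can therefore supply an admission score and several correlated post-operative scores for WOMAC and the quality-of-life scale.

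**Analysis.** Under Statistical analysis, "For continuous and binary data, the mean difference (MD) and odds ratio (OR) effect measures will be used". The chi-square and unpaired t-tests "will be performed to evaluate whether the null hypothesis can be refused". For a continuous patient-reported score, the t-test is the only test named. Implant accuracy is described separately, as deviation from the optimal alignment. No model using the admission score or earlier visits appears, and no visit is singled out for the comparison.

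**Sample size.** The calculation concerns WOMAC total: "Assuming a true difference in means between the test and the reference group of 5 units", SD 20, and 198 per group "to achieve a power of 80% and a level of significance of 5" percent. The total of 396 is 2 × 198, with no allowance for loss.

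**Awareness of arm.** According to the Discussion, "Patients will be informed in regard to the nature of the surgery (freehand or robotic) during their postoperative inpatient stay". This precedes the 6-week questionnaire.

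**The concern.** The design collects repeated scores, but the named test uses one score per patient. Two things follow.

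1. **Precision.** Admission and 6-week scores predict the 12-month score. A test that ignores them has a larger standard error than the data allow.
2. **Exposure to selective loss.** Suppose the t-test is applied at 12 months to the values on hand. A patient seen at admission and 6 weeks but absent at 12 months then adds nothing, although the 6-week score may show how that patient was faring. If poor early results lead to absence more often in one arm, the two groups of remaining patients differ for reasons other than surgery. Such loss is possible here: patients know their arm, scores are taken at appointments, and the gaps between visits are 46 weeks (52 − 6) and later 24 months.

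At stake is the WOMAC comparison on which the trial is sized, where a distortion of one or two points is not small beside 5.

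**Working it through.** **Inputs from the protocol:** 198 per arm, SD 20, planning difference 5, 80% power, 5% significance (sidedness not stated).

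**Assumed inputs** (the protocol gives none): 17% missing at 12 months; correlations of 0.5 (admission and 6 weeks), 0.4 (admission and 12 months) and 0.6 (6 weeks and 12 months).

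**1. The protocol's own figure.** n per arm = 2(z_α + z_β)² SD²/difference².
- One-sided 5%: 2 × (1.645 + 0.842)² × 400/25 = 197.9, so 198. This reproduces.
- Two-sided 5%: 2 × (1.960 + 0.842)² × 400/25 = 251.2, so 252. This does not.

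**2. Precision when loss is unrelated to outcome.** Observed per arm: 198 × 0.83 = 164.3.
- t-test: SE = 20 × √(2/164.3) = 2.21.
- Adding the admission score: the variance factor is 1 − 0.4² = 0.84, so SE = 20 × √(0.84 × 2/164.3) = 2.02.
- Adding the 6-week score too. Given admission, the 6-week variance is 1 − 0.5² = 0.75 and its covariance with 12 months is 0.6 − 0.5 × 0.4 = 0.40. The part explained by the 6-week score is 0.40²/0.75 = 0.213, leaving 0.84 − 0.213 = 0.627. SE = 20 × √[2 × (0.627/164.3 + 0.213/198)] = 1.98.

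Most of the gain comes from the admission score. The variance ratio (2.21/1.98)² is about 1.24. Power for 5 points at one-sided 5% is Φ(5/SE − 1.645): 73% for the t-test and 81% for the model. At two-sided 5% (1.960 in place of 1.645) it is 62% and 71%.

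**3. Bias of a t-test on observed 12-month values, no true effect.** By simulation, with loss depending on the 6-week score. The strength is about one unit of log-odds per SD (an odds ratio of 1.05 per point is 1.05²⁰ = 2.65 per SD). Absolute values in points:

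| Loss pattern | t-test | Likelihood estimate using the 6-week score |
|---|---|---|
| Unrelated to outcome, equal or 20% vs 10% | about 0 | about 0 |
| Same mechanism and same rate in both arms | about 0 | about 0 |
| Same mechanism, 20% vs 10%; correlation of 6 weeks with 12 months 0.3 / 0.5 / 0.7 | 0.5 / 0.8 / 1.1 | 0.1 or less |
| Same mechanism, 30% vs 10%; same correlations | 0.9 / 1.7 / 2.3 | about 0.1 or less |
| Selective in one arm only, 17%; correlations as assumed above | 1.7 to 2.0 | 0.1 or less |
| Opposite directions in the two arms (extreme), about 17%; correlations as assumed above | 3.5 to 4.0 | 0.1 or less |

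**4. Where the model does not protect.** The right-hand column is favourable by construction, because loss was made to depend on an observed score. If loss in one arm (17%, the same odds ratio) depends on the 12-month score itself, the t-test bias is about 2.9 points and the likelihood estimate keeps about 1.9.

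**The case against.** **Silence is not a rule.** A reader might infer that the protocol tests each visit separately on attenders and drops anyone who misses a visit. It says none of this, and imputation before the t-test is not ruled out. Analysis sets and missing-data rules are commonly left to a full protocol or SAP, which are not shown. This stands: the absence of such rules is no finding, and the bias is conditional. It does not remove the point about the test that is named. Substituting a longitudinal model would change that choice, not merely add detail to it.

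**Outcome-related loss alone does not bias the t-test.** A reader might think that it does. With no true effect, the same mechanism at the same rate in both arms gave no bias. Loss must also differ by arm.

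**The large figures need severe assumptions.** False-positive rates of 14% to 45% can be produced, but only with strong selection in one arm or opposite selection in the two. With the same mechanism and 20% against 10% loss, the rate is roughly 7%. Knowing one's arm makes differential loss possible; the protocol does not show it, and its Discussion links that knowledge to detection bias. This stands, and the severe scenarios should not be the headline.

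**The model is not a cure.** This also stands, as step 4 of the working shows.

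**Conclusion.** The point holds as one about the chosen test. For scores measured repeatedly, the protocol names a test that uses neither the admission value nor earlier visits. The cost in precision does not depend on selective loss: a standard error of about 2.2 against 2.0 points, under the assumed correlations of 0.4 to 0.6 and 17% loss.

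The bias is a conditional risk. It requires analysis of observed values only, and loss that is related to outcome and differs by arm. Its size is then about 0.5 to 1.1 points for 20% against 10% loss under one mechanism, and about 2 points with selective loss in one arm only. It approaches the 5-point planning difference only in extreme cases. The protocol does not support a statement that the WOMAC comparison is biased. The change is worth making because it is cheap and uses data already planned.

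**What to change.** In Statistical analysis, replace the unpaired t-test for WOMAC and the quality-of-life scale with one linear mixed model for repeated measures. Terms: arm, visit, arm-by-visit, admission score and admission score-by-visit, with unstructured covariance. Include all randomised patients with any post-operative score. Name one visit in advance and make the arm contrast at that visit the test.

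This analysis set conflicts with the rule under Surgical procedures and rehabilitation protocol that departures from the planned surgery or rehabilitation lead to exclusion from the study. The two must be reconciled in the text.

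**Cost:** wording only. No new data are needed, and the planned software fits such models. **Downside:** the model assumes that loss is explained by observed scores. Where loss depends on the unobserved later score, it reduces the bias but does not remove it.

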## Introduction

Total knee arthroplasty (TKA) aims to restore knee pain and function, and improve the quality of life of patients [1–3] with end-stage osteoarthritis (OA) [4]. However, between 2 and 20% of patients who underwent TKA reported restricted motion and anterior knee pain [1, 5, 6]. These complications could arise from a non-optimal alignment of implant components [2, 7]. In this context, the introduction of robotic-assisted TKA is supposed to improve the accuracy of component positioning and to match more precisely patients’ anatomy and biomechanics [8]. Robotic TKA has been introduced to improve component alignment [9–11], impacting favourably on postoperative pain, hospitalisation, long-term implant survival [12, 13], and patient satisfaction [14]. However, the advantages of robotic surgery over conventional freehand TKA are still unclear, and high quality clinical investigations on large scale are necessary. Therefore, a single-blind randomised controlled trial will be conducted to evaluate TKA using the CORI robotic system (Smith & Nephew PLC, London, Great Britain). The primary outcome of interest is to compare robotic-assisted TKA versus the conventional freehand TKA in terms of patient-reported outcome measures (PROMs), length of hospitalisation, blood values, blood transfusion units, and range of motion. The second outcome of interest is to evaluate the accuracy of component positioning of robotic-assisted TKA compared to the conventional TKA.

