**Fig. 1 Fig1:**
[figure not shown]
Set up of follow-ups and data extraction

The second outcome of interest will be to compare implant positioning between robotic and conventional TKA. Implant positioning will be evaluated using anteroposterior plain radiographs of the leg using the software MediCAD Knie 2D (mediCAD Hectec GmbH, Altdorf, Germany), which is used to perform surgical planning of hip, knee, shoulder, trauma and spine surgery. The imaging references to assess implant positioning are shown in Fig. 2. An explanation of the main imaging references used is shown in Table 2.

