**Fig. 2 Fig2:**
[figure not shown]
Imaging references, illustrating the main axes and reference angles

**Table 2 Tab2:** Imaging parameters

Abbreviation	Definition	Mean	Range	Description
mLDFA	Mechanical lateral distal femoral angle	88°	85–90	Angle between the lateral femur and the proximal femoral joint
mLPFA	Mechanical lateral proximal femoral angle	90°	85–95	Angle between the mechanical femoral shaft axis and the orientation line through the centre of the femoral head and the tip of the greater trochanter
m/aLDTA	Mechanical/anatomical lateral distal tibial angle	89°	86–92	Angle between the mechanical axis of the tibia and the tibial plafond, measured on the lateral side
m/aMPTA	Mechanical/anatomical medial proximal tibial angle	87°	85–90	Angle between the mechanical axis of the tibia and the tibial plateau knee joint line, measured on the medial side
JLCA	Joint line convergence angle	1.5° medial	0–3	Interaction of the intra-articular deformity arising from the osteoarthritis and the surrounding soft tissue laxity
MAD	Mechanical axis deviation	10 mm medial	3–17	Distance from the centre of the knee joint and the line of the mechanical axis
AMA	Anatomical-mechanical-angle	6°	5–7	Angle between anatomical and mechanical femoral axes

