### Surgical procedures and rehabilitation protocol

All patients shall receive a 1.5 g single administration of intravenous cefuroxime at induction of anaesthesia. A femoral nerve block shall be used for pain control and maintained for 48 h. A tourniquet 120 mmHg over the systolic arterial pressure shall be used. All surgeries will be performed using a standard medial parapatellar approach. A restricted kynematic alignment will be performed to all TKA. All components will be implanted following manufacturer instructions using the Smith & Nephew Legion Genesis II, with a posterior stabilised polyethylene liner insert. Both femoral and tibial implants will be cemented using Palacos cement (Heraeus Medical GmbH, Wehrheim, Germany). At the end of the procedure, 1 g of tranexamic acid will be injected intra-articularly. One closed suction deep drain and one open suction subcutaneous drain shall be used for the first 48 h. Anti-thrombotic prophylaxis with Rivaroxaban, 10 mg daily for 6 weeks, will start 12 h after the index procedure. Physiotherapy will follow standard protocols [21]. Patients will be followed by a team of physiotherapists during hospitalization from the first postoperative day. In the absence of complications or other medical reasons who prevent discharge, the standard length of hospitalisation at our institution is 5 days. Moreover, from POD-2, each patient will undergo two sessions of physiotherapy daily using continuous passive motion (CPM) for 60 min per session to flex and extend the knee joint. The physiotherapist will increase the range of motion at each. Patients shall be discharged when they shall have reach at least 80° of flexion. Starting from POD-2, patients will start to walk under physiotherapeutic supervision, and on POD-4 they shall start to ascend and descend stairs. A personalised outpatient or inpatient rehabilitation program will be set for every patient for a minimum of 3 weeks. Deviation from the planned surgical procedure and rehabilitation protocol shall warrant exclusion from the study.

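### The accuracy outcome is summarised by a group-level standard deviation that the planned t-test and chi-square test do not compare; a per-patient absolute deviation would fit both tests

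*Protocol article*

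**What the plan says.** The Introduction defines the outcome as accuracy: "The second outcome of interest is to evaluate the accuracy of component positioning of robotic-assisted TKA compared to the conventional TKA". Outcomes of interests words it as positioning: "The second outcome of interest will be to compare implant positioning between robotic and conventional TKA". Measurements come from anteroposterior leg radiographs, and Table 2 lists the imaging parameters.

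The sentence in Statistical analysis that deals with accuracy begins "To evaluate the accuracy of implant positioning of robotic versus conventional TKA with regards to the pre-operative planning" and continues "the standard deviation from the optimal implant alignment according to the patient anatomy will be evaluated". It does not say whether the standard deviation is taken about the arm mean or about the target.

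The same section names mean difference and odds ratio as effect measures, with 95% confidence intervals. For testing it says: "Both *χ*^2^ and unpaired *t*-test will be performed to evaluate whether the null hypothesis can be refused". It names no ratio of SDs or variances and no test for one.

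Two related places matter. Surgical procedures and rehabilitation protocol states that "A restricted kynematic alignment will be performed to all TKA". Table 2 describes the mechanical lateral distal femoral angle (mLDFA) as "Angle between the lateral femur and the proximal femoral joint".

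**The concern.** An accuracy outcome has to capture two things: how far an arm is off target on average, and how widely its knees scatter around the target. The Discussion expects the robotic system to help with both, through higher accuracy and less variation in component position. The quantity named for the outcome and the tests named for the trial do not fit together. The quantity is a group summary, while the tests compare means and proportions built from one value per patient.

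An analyst following the text would have to choose. One option is to report two SDs side by side with no formal comparison. The other is to run the t-test on signed deviations, which answers a different question. On the second route, a real reduction in scatter, which is one of the benefits the protocol expects, could be reported as no difference.

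**Working it through.** **Inputs.** The documents give no alignment SD, offset or outlier cut-off, so there is no accuracy figure to reproduce. The only input they supply is n = 198 per arm (Sample size evaluation, set for WOMAC). That number reproduces at one-sided 5%: 2 × 20² × (1.645 + 0.842)² / 5² ≈ 198. This is used only as the n below. All SDs, offsets and the 3° cut-off are assumptions, and errors are taken as normal.

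**Step 1: what the stated SD measures.** Let e be achieved minus target angle, with arm mean m and standard deviation s.

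- About the arm mean, the SD is s and does not depend on m.
- About the target, it is √(m² + s²). With m = 3° and s = 1.5° this is √(9 + 2.25) = 3.35°, against 1.5° in an arm with no offset.

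The second reading therefore registers an offset. Either way there is one value per arm, and no mean difference or odds ratio can be formed from it at patient level.

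**Step 2: t-test on signed deviations, arms differing only in spread.** Take m = 0 in both arms, with s = 1.5° and 2.0°. The expected mean difference is 0, so the test rejects at its nominal rate: 5.0% in 20,000 simulated trials.

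**Step 3: the same data as absolute deviations.** For m = 0, the mean of |e| is s√(2/π) and its variance is s²(1 − 2/π).

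- Means: 1.5 × 0.798 = 1.20° and 2.0 × 0.798 = 1.60°; difference 0.40°.
- Standard error: √[(2.25 + 4.00) × 0.3634 / 198] = 0.107°.
- z = 0.399 / 0.107 = 3.72; power = Φ(3.72 − 1.96) = 0.96. Simulation gives 0.96.
- Share beyond 3°: 4.6% against 13.4%; a chi-square test on this has about 87% power.

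**Step 4: range over other assumed spreads, no offset.**

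| SD by arm | t-test, signed | t-test, absolute | Chi-square, share beyond 3° |
|---|---|---|---|
| 1.5° vs 2.0° | about 5% | about 96% | about 87% |
| 2.0° vs 2.5° | about 5% | about 82% | about 70% |
| 1.5° vs 2.5° | about 5% | about 100% | about 100% |
| 2.0° vs 2.0° (no difference) | about 5% | about 5% | not applicable |

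The last row shows that the t-test on absolute deviations keeps its size.

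**Step 5: arms differing in offset.** With m = 3° against 0° and s = 1.5° in both arms, the standard error of the signed mean difference is 1.5 × √(2/198) = 0.151°, so t ≈ 3 / 0.151 = 19.9. The signed test sees this offset. Mean absolute deviation is 3.03° against 1.20°, so the absolute test sees it too. The signed test misleads in another case: equal and opposite offsets, say +2° and −2° with the same SD. It would reject although the two arms are equally inaccurate, while their mean absolute deviations are the same.

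**The case against.** The strongest reply is that the wording says deviation from the optimal, not from the arm mean. Read that way, the measure includes offset, as Step 1 shows. The plan also applies mean difference, confidence interval and t-test to continuous data in general, and Outcomes of interests lists implant positioning among the items to be compared. A reader might infer that the trial could declare the arms equally accurate while one is consistently several degrees off. The documents do not support that: a one-arm offset shows both in the deviation about the target and in the signed t-test. This part of the reply stands.

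It can also be said that the authors may have meant a per-patient absolute deviation, for which the planned t-test is valid, and that the choice of angles, sign convention and cut-off belongs in an analysis plan that is not shown. That such details are absent is indeed no finding. But the article does state a metric, and as stated it is a standard deviation, which the tests named beside it do not compare.

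Two further inferences should be resisted. The references to pre-operative planning and to the optimum for the patient's anatomy may be one target clumsily described; they need reconciling but are not shown to conflict. And although Table 2 lists hip-level and ankle-level angles (mLPFA, LDTA), nothing says that these will be tested between arms.

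**Conclusion.** The point holds in limited form. The stated accuracy metric is a group-level summary that neither planned test compares, and the obvious substitute, a t-test on signed deviations, has no power against a difference in spread: about 5% rejection against 82% to 100% on absolute deviations over the assumed SDs, with 198 per arm. These figures rest on assumed normal errors, zero offset and assumed SDs, so they show the mechanism and do not predict this trial's results. If the SDs were reported by arm, a reader could still see a difference in spread, but without a test or interval. The outcome is the second one, not the WOMAC outcome used for the sample size, and the remedy is nearly free, so the wording should be changed before analysis. The mLDFA description in Table 2 is a separate, editorial correction: the parameter's name says distal while its description says proximal.

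**What to change.** 1. Define accuracy for each patient as the absolute difference, in degrees, between the achieved angle and that patient's target, for named knee-level angles of Table 2 (for example mLDFA and MPTA).
2. State one target definition, worded identically for both arms, by reconciling the pre-operative plan with the optimum for the patient's anatomy. Since the Discussion describes real-time planning by the robotic system, say at what time point the target is fixed. Which target to use is for the investigators to decide.
3. Compare the mean absolute deviation by the planned unpaired t-test, with mean difference and 95% confidence interval. Compare the share of knees beyond a threshold set in advance by chi-square, with the odds ratio.
4. Report the signed mean deviation and the SD by arm separately, so that offset and scatter can each be seen.
5. Correct the Table 2 description of mLDFA.

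The cost is one computed column and a few extra summary lines, from the same radiographs and software, with no new measurement.
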